##### SmArt-E app

As early as the in-person treatment starts, patients shall also use the app for regular exercises, PA, and education at home. The app additionally holds a chat and videoconference feature to connect patients and their physiotherapists on demand. Moreover, the app features support behaviour change through weekly exercise and PA goals, scheduling of exercise, self-monitoring of one’s performance and automated feedback on progress including positive reinforcement through compliments for goal achievement. Figures 2 and 3 show the today view and the exercise feature of this app as of December 2022, respectively.

**Fig. 2 Fig2:**
[figure not shown]
Screenshot of the SmArt-E app showing the exercise feature

**Fig. 3 Fig3:**
[figure not shown]
Screenshot of the SmArt-E app showing the today view

##### Behaviour change techniques

Physiotherapists are introduced to strengthen participants’ self-efficacy regarding independent training and PA. To support both phases, the initiation as well as the maintenance of regular exercise and PA by patients, behaviour change techniques are incorporated into the intervention as part of the in-person physiotherapy sessions as well as the subsequent smartphone-assisted training phase. Based on effective behaviour change techniques [24], physiotherapists guide participants to set long-term personal goals, to make action plans for exercises and PA (i.e., action planning) and to establish them as habitual routines by implementing them according to personal preferences and easily compatible with daily life. This planning is based on providing basic information on OA, pain and chronic disease management. Furthermore, possible barriers and problem-solving strategies to deal with them in the sense of coping planning are discussed.

#### Training of physiotherapists to provide the SmArt-E intervention

A structured training builds on existing knowledge and competences to qualify physiotherapists in the SmArt-E intervention. Therefore, an 8-hour training (including pre- and post-processing) in groups of up to ten physiotherapists on the study itself, the components of the intervention, the behaviour change techniques in use and an app introduction will be conducted. This will be followed by a 1.5-hour refresher course after 3 months after the intervention start to expand knowledge on techniques for behaviour and lifestyle changes. Learning objectives for the initial training are to become familiar with the (1) exercise programme and educational content of the SmArt-E intervention, (2) possibilities to adapt, supervise and individualize the exercise programme and daily PA, (3) features of the app, (4) blended care approach, and (5) self-management strategies in SmArt-E. Moreover, physiotherapists should be able to (6) independently adapt the preselected exercises of the app to the individual needs and preferences of the patients, and (7) to empower participants to perform physical exercises on their own, assisted by the app. Furthermore, they should be trained (8) to support participants to cope with their disease independently and (9) to perform health-enhancing PAs regularly (graded or non-graded PA programme). The learning objectives of the refresher course encompass (1) additional motivational strategies, (2) specific coping strategies to enable participants to integrate self-managed exercises into their daily life with adequate intensity. Furthermore, physiotherapists should (3) support participants remotely in terms of exercise programme design and educational content. Additionally, they shall (4) support participants in behavioural and lifestyle changes, (5) promote PA, and (6) enable participants in the retention of behaviour change and development of coping skills in the long term, e.g., strategies to resolve emerging problems.

#### App adaptation and enhancement: thinking-aloud method

The study app is being further developed based on an existing Dutch app (e-Exercise) in close collaboration between the research team and the technical partner *HealthTrain* (Utrecht, Netherlands). Once the app is ready for implementation (Android and iOS), we use the thinking-aloud procedure to assess its usability. Therefore, five randomly selected participants are to accomplish selected tasks within the app while expressing their thoughts aloud. The feedback is recorded with the help of audio recordings and evaluated in terms of qualitative content analysis. This sample size is sufficient to log 85% of the usability problems [39].

### Usual care

The control group receives usual care, which might comprise physiotherapy sessions, but also other treatments like injections, acupuncture, or no treatment at all. An additional 45-minute consultation with a physiotherapist on PA-recommendations for OA including informational material, access to the app, and a smartphone if sought, is offered following the final assessment.

### Outcomes (measures)

Table 4 shows descriptive variables, as well as primary and secondary outcomes. Assessors receive 2 h of training on all aspects of the assessment to ensure a high level of standardization.

**Table 4 Tab4:** Overview of outcome measures, screening instruments and descriptive measures over the course of the study

		PS	TS	T_**0**_	T_**1**_	T_**2**_
	*Sociodemographic and health-related data*					
	Date of birth, age, and sex			X		
	School-leaving qualification; academic grades; employment; living conditions (i.e., living alone/ in a nursing home); monthly net income;			X		
	German-speaking		X			
	*Medical and medication information*					
	Height; weight; body mass index; health status; co-morbidities; walking aids			X		
	OA-related treatment history and surgery; previous joint replacement			X		
	Screening for study eligibility and absence of contraindications	X	X			
	*Physical functioning*					
P	Hip Disability and Osteoarthritis Outcome Score (HOOS)			X	X	X
P	Knee injury and Osteoarthritis Outcome Score (KOOS)			X	X	X
	*Pain and tiredness*					
P	Numeric rating scale (NRS)			X	X	X
	*Physical capacity*					
S	Modified Y-Balance-Test			X	X	X
S	30-Second Chair Stand Test (30s CST)			X	X	X
	*Physical activity*					
S	ActiGraph 3 GT3X tri-axial accelerometers and activity diary			X	X	X
S	Activity questionnaire			X	X	X
	*Action planning and coping planning*			X	X	X
S	*Questionnaire*					
	*Health-related quality of life, health status*					
S	European Quality of Life 5 Dimensions 5 Level Version (EQ-5D-5L)			X	X	X
S	Patient Global Assessment (PGA)			X	X	X
S	Subjective change of health status				X	X
	*Coping strategies*					
S	Pain Catastrophizing Scale (PCS)			X	X	X
	*Psychosocial status*					
S	Self-Report Behavioral Automaticity Index (SRBAI)			X	X	X
S	Patient Acceptable Symptom State (PASS)			X	X	X
S	Arthritis Self-Efficacy Scale (ASES)			X	X	X
	*Satisfaction*					
S	ZUF-8 questionnaire + 1 item for patient perspective on satisfaction with treatment results				X	X
	*Usability*					
	System Usability Scale (SUS)				X	
	mHealth App Usability Questionnaire (MAUQ)					X
	*Health literacy*					
	European Health Literacy Survey (HLS-EU-Q16)			X		
	eHealth Literacy Scale (eHEALS)			X		
S	Movement-related Health Literacy			X		X
	*Technology readiness*					
	Technology commitment			X		
	*Health Economic Evaluation* Questions on out-of-pocket expenses and resource use			X		X
	*Health insurance routine data* Data comprise information on costs, diagnoses, procedures and the scope of services, e.g., number of doctor visits, length of hospital stay.			X		X
	*Interaction between user and intervention*					
	Thinking Aloud-Approach			X		

*Abbreviations*: *PS* pre-screening by general practitioner, *TS* telephone screening, *T*_*0*_ baseline assessment, *T*_*1*_ 3-month assessment, *T*_*2*_ 12-month assessment, *P* primary outcome measure, *S* secondary outcome measure

#### Primary outcomes

The primary outcomes are physical functioning and pain. Physical functioning will be assessed using the subscale “function in daily living” of the Hip Disability and Osteoarthritis Outcome Score (HOOS) [40] or of the Knee injury and Osteoarthritis Outcome Score (KOOS) [41], depending on the index joint. Both questionnaires are validated in German language comprising 40 and 42 items, respectively, distributed across the five subscales pain, symptoms and function in daily living, sports activities and quality of life [40, 41]. Each item is scored on a five-point Likert scale (0 = extreme symptoms/problems; 4 = no symptoms/problems). Hence, lower scores indicate higher impairments. Pain will be assessed using an 11-item numeric rating scale (NRS) [42, 43]. Patients select a number (0–10 integers) that reflects their pain intensity best on a horizontal bar [43], ranging from zero (“no pain”) to ten (“worst pain imaginable”) and related to the previous 24 hours [42, 43].

#### Secondary outcomes

##### Knee−/hip-related health, symptoms, and functionality

The HOOS/KOOS subscales pain, symptoms, sports activities and quality of life of the will be assessed as secondary outcomes of the study [40, 41].

##### Physical performance

The *Lower Quarter Y-Balance Test (YBT)* is a simplified version derived from the Star Excursion Balance Test that represents a valid and reliable assessment of lower extremity dynamic neuromuscular control among patients with OA [44, 45]. The YBT uses a testing kit and a revised protocol to improve reliability and screening speed [45, 46]. Participants perform the test while standing in a single-leg stance and pushing a rectangular box with their foot along the three axes of the kit. Based on three attempts into each direction and on each leg, the greatest reached distance in relation to the individual leg length as well as the according between-limb asymmetry will be assessed to evaluate the intervention effects.

The *30-Second Chair Stand Test* (30-CST) is a valid and reliable lower extremity physical performance measure in which participants stand up and sit down as often as possible within 30 seconds with their arms crossed in front of their chest. The 30-CST demonstrate better responsiveness in detecting physical performance changes compared to other measures and is appropriate for older adults over the age of 60 years [47].

##### Physical activity (PA)

Daily PA will be assessed using ActiGraph GT3X triaxial accelerometers [48], successfully used in previous clinical trials including patients with knee and/or hip OA [49]. Participants wear the accelerometer attached to a waist belt for ten consecutive days throughout their waking hours, except for showering or swimming. Additionally, participants will be asked to complete a short activity diary including wearing time, unusual activities, or activities difficult to detect, as well as reasons and duration for removal of the device. Data will be recorded at a sampling rate of 100 Hz. After returning the accelerometer and diary, data will be downloaded, processed, and analysed, for which the Freedson thresholds will be used. 0–99 counts per minute (CPM) indicate sedentary behaviour, while values between 100 and 1951, 1952–5724, 5725–9498, and values ≥9499 CPM indicate light, moderate, vigorous, and very vigorous PA, respectively [50]. Valid PA assessments require a minimum wear time of at least 7 days, 10 h per day [51].

Additionally, we will use a questionnaire on daily PA focusing on leisure and work, comprising nine items that are part of the “German Health Update” (GEDA) study of the Robert Koch Institute [52], and a single question derived from the Global Physical Activity Questionnaire developed by the WHO on daily sitting time [53].

##### Action & coping planning

Planning can be divided into action planning and coping planning, and can be considered a prospective self-regulatory tool that can help turning goals into behaviour [54]. Two scales measuring action planning and coping planning [54] will be used following an adaptation to planning regular PA, consisting of three items each that are rated on a four-point Likert scale ranging from “completely disagree” [1] to “totally agree” [4]. The action planning scale assesses the extent to which a person has made specific plans about when, where, and how they will be physically active on a regular basis. The coping planning scale assesses the extent to which a person has made specific plans about how they will cope with potential barriers to regular PA.

##### Quality of life/health status

The *European Quality of Life 5 Dimensions 5 Level Version (EQ-5D-5L)* questionnaire is valid and reliable for the assessment of the health status in clinical and health economic studies [55, 56]. The EQ-5D-5L covers five domains (mobility, self-care, usual activities, pain/discomfort, and anxiety/depression). Further, it includes five levels referring to the severity of restrictions, based on which the EQ-5D-5L-index is determined that expresses the health status ranging from zero to one with one indicating the best possible health status. This index will be used to calculate Quality Adjusted Life Years (QALYs) [57].

The *Patient Global Assessment (PGA)* is used to quantitatively assess the general health status using a single question from the EQ-5D-5L health questionnaire in its German version [56, 58, 59]. Patients score their current global health status on a visual analogue scale ranging from 0 to 100 mm using the anchors worst and best possible. The *subjective health status change* will be assessed regarding the change in general, the change in pain, and the change in physical functioning (walking). According to Angst et al. (2017) [60], participants will be asked: “How is your health (pain, physical function) today compared to three months ago regarding OA in your affected knee joint or hip joint?”. Response options include the anchors “much better”, “slightly better”, “about the same”, “slightly worse”, and “much worse” [60].

##### Coping strategies for pain

Pain catastrophizing will be assessed using the *Pain Catastrophizing Scale* (PCS) comprising the three subscales helplessness, magnification, and rumination [61]. In 13 items, participants rate the frequency of pain experiences on a five-point Likert scale ranging from zero (mild symptoms) to four (worst symptoms). Adding the individual items results in a total score ranging from zero to 52. Higher scores indicate more pain catastrophizing characteristics. A reliable and validated German version of the PCS is available [62].

##### Psychosocial status

The *Self-Report Behavioural Automaticity Index* (SRBAI) is a four-item subscale of the Self-Report Habit Index (SRHI) that reliably captures habitual behaviour patterns and can be used to predict future behaviour or to track habit formation or disruption [63, 64]. Being more succinct than the SRHI, the SRBAI is easier to administer, but still sensitive to effects that characterize habits [63].

The *Patient Acceptable Symptom State* (PASS) uses a single question to assess the level of symptoms at which patients consider themselves healthy [65]. The PASS will be assessed using the global question: “Assuming you remain in the present condition for the next few months, do you believe that your current state is acceptable?”. A dichotomous yes/no response option indicates the patient’s satisfaction with their current symptoms state.

The *Arthritis Self-Efficacy Scale* (ASES) was originally developed as a 20-items questionnaire to assess OA-specific self-efficacy in patients and to explain changes resulting from (educational) interventions [66]. A shortened and validated German version comprises eight items rated on a visual analogue scale ranging from one (very uncertain) to ten (very certain), with higher scores indicating increased perceived efficacy [67].

##### Physical activity related health competence

The construct *PA-related health competence* comprises the three domains movement control, control competence, and self-regulation, required to perform health-promoting PA on a regular base [68]. A shortened 14-items version derived from the validated original instrument is available in German language for assessing PA-related health literacy in rehabilitation and prevention settings [69, 70].

##### Patient satisfaction

The *ZUF-8* measures global, unidimensional patient satisfaction with received care [71]. It covers eight items that are rated on a four-point Likert scale ranging from one (least favourable) to four (most positive characteristic), available in German language with excellent psychometric properties [71, 72]. For evaluating the app satisfaction, participants of the intervention group will respond to three additional questions, analogously to the original ZUF-8 items, but related to the app. The questions are: 1. “To what extent did the app meet your needs?”, 2. “Would you recommend the app to a friend if they needed similar help?” and 3. “Would you use the app again if you needed help?”. To add the patient perspective on their satisfaction with the treatment results, the following item will accompany the ZUF-8: “How satisfied are you with the results of your treatment?”, rated on a five-point Likert scale ranging from “very satisfied to very unsatisfied” [73].

#### Covariates

##### Health literacy

Health literacy will be assessed using the *European Health Literacy Survey* (HLS-EU-Q16) [74]. The questionnaire addresses the four dimensions of general health literacy encompassing access, understanding, assessment, and use of health information in disease prevention, health promotion, and healthcare [74]. The participants rate tasks and activities related to healthcare, disease prevention, and health promotion on a four-point Likert scale. The *eHealth Literacy Scale* (eHEALS) is developed to meet the growing requirement to assess digital health literacy [75]. The questionnaire includes eight items and assesses the perception of knowledge and skills in finding, evaluating, and using electronic health information on a five-point Likert scale. eHEALS is available in German language [76] and represents a valid and reliable scale for perceived measurement of eHealth literacy among adult populations and patients with chronic diseases [77].

##### Technology commitment

Technology commitment is thought to predict the successful use of new technologies, particularly at older ages. A 12-item scale for measuring *technology commitment* with good psychometric properties has been developed and validated in German language [78]. The scale addresses three different facets of handling technology, comprising technology acceptance, technology competence beliefs, and technology control beliefs.

### Participants

#### Participant timeline

Study participation begins with an initial assessment (t0), followed by randomization of participants. The SmArt-E intervention expands over 12 months with follow-up assessments at 3 (t1) and 12 months (t2) after the start of the intervention and starting with in-person physiotherapy. A refresher session is held after 6 months (see Fig. 4).

**Fig. 4 Fig4:**
[figure not shown]
Patient flow of the SmArt-E study

#### Sample size

We aim to recruit 330 patients, equally distributed among the intervention and control group. The sample size calculation assumes an effect size of Cohen’s *d* = 0.34 for the comparison of the *SmArt-E* intervention and usual care for the primary outcomes of pain and physical functioning after 12 months. This assumption is derived from a recent meta-analysis involving 44 clinical studies evaluating internationally established, comparable exercise therapy compared to *do-nothing* or *sham* control conditions and a dropout rate of 15%, resulting in effect sizes of *d* = 0.49 for pain and *d* = 0.52 for physical functioning [23]. A comparable RCT with digital support demonstrate similar results, in which the authors find a greater pain reduction of approximately − 1.0 (±2.3) points on a 11-point NRS in the intervention group compared with the control group, corresponding to an effect size of *d* = 0.44 [33]. Regarding physical functioning, an effect of *d* = 0.66 is observed. We assume smaller effect sizes for the SmArt-E intervention as this will be compared to current usual care, which should be more effective than *Do-Nothing* or *Sham*. Based on a *t*-test for independent samples, one-sided *α* = 0.05 and *β* = 0.80, a sample size of *n* = 274 is necessary when considering the number of outcomes and Bonferroni corrections (*n* = 137 per group). Target sample size is increased to *n* = 330 to compensate for dropouts of up to 20%. Additional power is gained by statistically accounting for age, gender, and the baseline value of the respective outcome.

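### The target of 330 covers dropout of about 17%, not the stated 20%: a 20% loss leaves 264 patients, 10 fewer than the 274 required (minor)

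*Protocol article*

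**What the plan says.** The Sample size section (Methods, Participants) plans on a standardised effect of 0.34 for each of the two primary outcomes, pain and physical functioning at 12 months. It uses an independent-samples t-test with a one-sided α of 0.05, corrected for two outcomes, and on that basis finds that "274 is necessary when considering the number of outcomes and Bonferroni corrections", which it splits as 137 per group. The next sentence raises the target to "330 to compensate for dropouts of up to 20" per cent.

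The paragraph ends by noting that adjustment for age, gender and the baseline value of the outcome will add power. It gives no correlation or explained variance. The target of 330 is repeated in the Abstract, in Study design and in Table 1. The article states no inflation formula.

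**The concern.** A dropout allowance is a simple promise: if losses stay within the stated limit, the number completing still meets the requirement. Here the requirement (274), the limit (20%) and the target (330) all stand in one paragraph, and they cannot all be true.

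What is at stake is a stated planning margin. Anyone judging the completed trial against its protocol would regard a loss of 18% or 19% as within plan, although fewer than 274 patients would then remain.

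**Working it through.** **Inputs, all from the Sample size section:** d = 0.34; one-sided α = 0.05; two primary outcomes with Bonferroni correction; 0.80 read as power; 274 required (137 per group); target 330, split equally (165 per group); dropout up to 20%.

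**1. Reproduce the base figure.** Per-outcome α = 0.05/2 = 0.025, one-sided. The two-sample t-test (noncentral t) with d = 0.34 and power 0.80 needs 136.76 per group, so 137 per group and 274 in total. This matches the plan exactly. The normal approximation gives 136 per group. The base figure is sound, so the discrepancy lies in the step from 274 to 330.

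**2. Apply the stated dropout to the target.**
- 330 × (1 − 0.20) = 264, or 132 per group.
- 274 − 264 = 10 patients short.

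**3. Find the dropout that 330 does cover.**
- 330 − 274 = 56 patients can be lost.
- 56/330 = 1 − 274/330 = 0.1697, or 17.0%.

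**4. Find the target that 20% would need.**
- In total: 274/(1 − 0.20) = 342.5, so 343.
- With equal arms: 137/0.80 = 171.25, so 172 per group and 344 in total.
- This is 13 to 14 patients more than 330.

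**5. Look for a rule that gives 330.** 137 × 1.2 = 164.4, rounded up to 165 per group, gives exactly 330. The target is therefore consistent with adding 20% of the required number. Dividing the required number by 0.80 does not give it.

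**6. Effect on power** (d = 0.34, one-sided 0.025, unadjusted t-test, per outcome).

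| Evaluable per group | Power |
|---|---|
| 137 | 80.1% |
| 132 | 78.6% |

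The loss is about 1.5 percentage points. At 132 per group, 80% power needs d = 0.346 instead of 0.34.

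**7. Effect of baseline adjustment.** The article gives no correlation, so r is an assumption. With a baseline-outcome correlation r, the residual SD shrinks by √(1 − r²), and the effective d becomes 0.34/√(1 − r²). At 132 per group:

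| Assumed r | Power |
|---|---|
| 0 | 78.6% |
| 0.1 | 79.0% |
| 0.2 | 80.2% |
| 0.3 | 82.3% |
| 0.5 | 88.8% |

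**The case against.** The strongest reply is that the planned analysis is not the t-test behind the 274. The Statistical analysis section specifies analysis of covariance with baseline values as covariates, and the table above shows that a correlation of only about 0.2 restores 80% power with 264 patients. It also specifies an intention-to-treat analysis with multiple imputation or maximum likelihood, and both primary outcomes are measured at 3 months. Participants lost after that visit can therefore still contribute, and 264 fully lost-to-analysis completers is a worst case. Finally, the shortfall arises only if dropout exceeds 17%.

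All of this stands as an argument about size, and it is why the point is minor. It does not make the sentence correct. The 274 rests on an unadjusted test; the article presents covariate adjustment as a gain beyond the dropout allowance, not as the means of meeting it; and the text itself inflates for dropouts as lost. Rounding does not explain a gap of 13 to 14 patients.

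Three stronger readings are tempting, and the document does not support them:
- **Two conflicting dropout assumptions.** The paragraph also contains the words "sham* control conditions and a dropout rate of 15" per cent. A reader might take this as a second planning rate, but it sits in the sentence describing the cited meta-analysis. The only allowance attached to the target is 20%.
- **A proven multiplication error.** The match with 137 × 1.2 is exact, but no formula is given, so the cause is an inference. The shortfall does not depend on it.
- **Retention monitored against a wrong limit.** The article describes no retention threshold or alert, so this harm cannot be attributed to the plan.

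**Conclusion.** The point holds as a minor arithmetic inconsistency. The target of 330 tolerates dropout of about 17.0%, not 20%. At 20% it leaves 264 evaluable patients (132 per group), and unadjusted power per outcome is about 78.6% instead of 80%.

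The figures for 264, 17.0% and 343 to 344 rest only on the article's own numbers. The power figures also assume d = 0.34, one-sided 0.025 per outcome, equal loss in the two arms and no contribution from dropouts. The offset from baseline adjustment rests on an assumed correlation: 80% is regained at about 0.2 and exceeded above that. A reader might infer that the trial is underpowered for its planned primary analysis. The document does not support that, because the power of the adjusted analysis is not quantified and is plausibly above 80% even at 20% loss.

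**What to change.** Choose one of two corrections to the Sample size section:
- keep the target of 330 and state that it compensates for dropout of up to about 17%; or
- keep the 20% figure and state that it leaves 264 evaluable patients, with about 78.6% power per outcome before covariate adjustment.

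In the same paragraph, replace β = 0.80 with power (1 − β) = 0.80. Read literally, the present label means 20% power; the reproduced 274 shows that 80% power was used.

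The cost is wording only. Recruitment, conduct and analysis do not change, and the stated margin becomes slightly less generous. Raising the target to 343 or 344 would also reconcile the figures, but the size of the shortfall does not call for it.

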#### Randomization and blinding

At t0 (initial assessment) the assessors will allocate participants to the intervention or control group by block randomization using REDCap (Vanderbilt University, Nashville, Tennessee, USA), for which a 1:1 allocation ratio stratified by the affected joint (hip vs. knee), sex, and study centre will be applied. Participants of the intervention group will be treated in the nearest participating physiotherapy practice.

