#### Statistical analysis

The primary outcomes comprising physical functioning (HOOS/KOOS) and pain reduction (NRS) at 12 months from baseline are compared between the intervention and control group using Bonferroni-adjusted analysis of covariance with gender, index joint, allocation (individual/group treatment), baseline values (pain and physical functioning) and the study centre as covariates. In sub-group analyses, corresponding models will be applied only to patients with hip or knee OA and only to women or men, respectively. Wherever required, differences in the effects are tested by expanding the overall model with corresponding interaction terms. Study centre effects are studied in a similar way. A secondary analysis will examine intervention group differences in the time course of pain and physical functioning, including all assessment appointments and using mixed models. Effects on the secondary outcomes are investigated descriptively (and without Bonferroni correction) using appropriate regression models. The analysis is primarily based on the *intention-to-treat* principle. Missing values will be considered by multiple imputation and *maximum likelihood* principle, respectively. If large numbers of imputations will be necessary, a robustness analysis with alternative imputation strategies will be carried out. All statistical analyses are defined in a Statistical Analysis Plan prior to the completion of patient recruitment.

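### Age is named as a source of extra power in the sample-size section but is absent from the primary ANCOVA covariate list, so that part of the claimed gain is not delivered

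*Protocol article*

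**What the plan says.** In the protocol article, the Sample size section bases the number of participants on an independent-samples t-test and then closes with a remark on adjustment: "Additional power is gained by statistically accounting for age, gender, and the baseline value of the respective outcome". No amount is attached to this gain.

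The Statistical analysis section describes the primary comparison at 12 months as a Bonferroni-adjusted analysis of covariance "with gender, index joint, allocation (individual/group treatment), baseline values (pain and physical functioning) and the study centre as covariates". Age does not appear, and the list is not introduced as a set of examples.

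Two other places bear on the point. Table 4 shows age recorded at T0. The section on randomization and blinding describes "a 1:1 allocation ratio stratified by the affected joint (hip vs. knee), sex, and study centre will be applied", so age is not a stratification factor.

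**The concern.** Both sections concern the same two primary outcomes at 12 months, yet they name different adjustment variables. The mismatch runs both ways: the analysis section has index joint, individual/group allocation and centre, which the power remark does not name, and the power remark has age, which the analysis section does not. Only the second direction is a problem, because there the protocol claims a benefit that its own analysis does not collect.

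Age could plausibly carry some prognostic information. Entry is open above 38 years for knee and above 50 for hip osteoarthritis, with no upper limit. The variable is already collected, so its absence is not explained by lack of data. What is at stake is a small amount of precision, and agreement between the two sections on which covariates the primary model contains.

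**Working it through.** **Step 1. Reproduce the plan's figure.** Inputs from the Sample size section: d = 0.34, one-sided α = 0.05, Bonferroni correction, and 80% power (the article writes β = 0.80, read here as power). With two primary outcomes the level is 0.05/2 = 0.025 one-sided for each. Allocation is 1:1.

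- Normal approximation: n per group = 2(z₀.₉₇₅ + z₀.₈₀)²/d² = 2(1.960 + 0.842)²/0.34² ≈ 135.8, rounded up to 136, total 272.
- Exact t-test (noncentral t): 136.76, rounded up to 137 per group, total 274.

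The stated 274 is matched exactly with no covariate adjustment. No gain from age, gender or baseline is built into it.

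**Step 2. Compare the covariate lists.**

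| Variable | Sample size section | Primary ANCOVA |
|---|---|---|
| Baseline value of the outcome | yes | yes |
| Gender | yes | yes |
| Age | yes | no |
| Index joint | no | yes |
| Individual/group allocation | no | yes |
| Study centre | no | yes |

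**Step 3. Size of the forgone gain.** The article gives no correlation of age, or of baseline, with the 12-month outcomes. Assumptions: baseline-outcome correlation r_b from 0.3 to 0.6, and partial correlation of age with the outcome given the other covariates, r_a, from 0 to 0.2.

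Adding age multiplies the residual variance by (1 − r_a²). The reduction is 0 at r_a = 0, 0.1² = 1% at 0.1, and 0.2² = 4% at 0.2. Against 274 evaluable participants, the last two correspond to 274 × 0.01 ≈ 3 and 274 × 0.04 ≈ 11 participants.

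Power at 137 per group is approximately Φ(d√(137/2)/σ − 1.960), with σ² = (1 − r_b²)(1 − r_a²) on the standardised scale. With no adjustment this gives 80.3%.

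| r_b | Power, baseline only | Added by age, r_a = 0.1 | Added by age, r_a = 0.2 |
|---|---|---|---|
| 0.3 | 83.9% | 0.4 points | 1.4 points |
| 0.4 | 86.7% | 0.3 points | 1.3 points |
| 0.5 | 90.1% | 0.3 points | 1.1 points |
| 0.6 | 94.0% | 0.2 points | 0.8 points |

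Worked case, r_b = 0.3 and r_a = 0.2: σ = √(0.91 × 0.96) = 0.935; 0.34 × √68.5 = 2.814; 2.814/0.935 − 1.960 = 1.05; Φ(1.05) ≈ 85.3%, against 83.9% without age.

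If r_a were as high as 0.3, the gain would be 1.8 to 3.2 points over the same range of r_b. At r_a = 0 it is nil.

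**Step 4. Put it in proportion.** Baseline adjustment alone lifts power from 80.3% to between 83.9% and 94.0% under these assumptions, a gain of 3.6 to 13.7 points. Both sections include baseline, so most of the benefit described in the sample-size sentence is retained.

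**The case against.** The case against making much of this is strong, and most of it stands.

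- A reader might infer that the sample size relies on age adjustment. It does not: 274 is an unadjusted figure, and the sentence on extra power comes after it as an unquantified bonus. Leaving age out changes neither 274 nor the 330 recruitment target.
- A reader might infer that the protocol defines two rival primary models. It does not. The sample-size sentence is a remark on power. Only the Statistical analysis section names a method and a covariate list, and anyone asked for the primary model would take it from there. That section also defers to a Statistical Analysis Plan to be fixed before recruitment is complete. That plan is not shown and may settle the list.
- A reader might infer that chance imbalance in age biases the result. In a randomised comparison it does not: such imbalance is already covered by the error rate of the test. The three stratification factors are all in the model.
- The size of the loss rests on assumed correlations. It is zero if age adds nothing beyond the other covariates, and adjusting for index joint and centre may make up for it.

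What remains is that the article claims power from a variable its primary analysis does not use. That is a discrepancy in the published text, and a plan not shown does not remove it.

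**Conclusion.** The point holds as a minor inconsistency. The primary ANCOVA omits a covariate that the Sample size section credits with added power, so that part of the claimed gain is not realised by the analysis as written. Under an assumed partial correlation of 0 to 0.2, the forgone gain is 0 to 4% of residual variance, or roughly 0 to 1.4 points of power. Sample size, type I error and the validity of the comparison are unaffected. Correcting it is worthwhile because the variable is already collected, the protocol itself names it as useful, and the change costs almost nothing.

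**What to change.** Add age, as a continuous variable measured at T0, to the covariates of the primary ANCOVA in the Statistical analysis section, so that the analysis matches the sample-size statement. The change should be made before outcome data are examined by arm. It costs one degree of freedom and no additional data collection, and the sample size needs no recalculation.

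If the sponsor does not want age in the model, the alternative is to delete it from the sentence in the Sample size section. That also removes the discrepancy, but gives up whatever gain age would bring.

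This point gives no ground for removing the individual/group allocation term or any other listed covariate. Those should stay as they are for the purpose of this correction.
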